#### Self-Reported Balance Confidence

The Activities-specific Balance Confidence Scale is a self-report measure of balance confidence [75]. Individuals are asked to rate their confidence in completing 16 common tasks without losing balance, on a scale from 0% (no confidence) to 100% (complete confidence). The Activities-specific Balance Confidence Scale has demonstrated excellent test-retest reliability (*r*=0.92) and has been shown to have better scale responsiveness than the Falls Efficacy Scale when used with community-dwelling older people aged 65-95 years [75].

#### Pattern of Mobility

The Life-Space Assessment measures a person’s usual pattern of mobility during a 1-month period, documenting mobility based on how far and how often a person travels and any assistance required [76]. The Life-Space Assessment has excellent test-retest reliability (ICC 0.96) [77] and has been used in longitudinal studies of aging [76] to assess mobility frequency and distance. It will be used to determine baseline levels of self-reported mobility and to track changes that occur with the interventions.

#### Knowledge, Skill, and Confidence for SM

The Patient Activation Measure is a 13-item measure of the patient’s level of knowledge, skill, and confidence for SM [78]. Raw scores (13-52) are converted into activation scores (0-100) with higher scores indicating greater patient activation. The Patient Activation Measure has a MCID of 0.5 points [79] with high test-retest reliability (ICC 0.85) and evidence of validity against a classification of individuals’ level of activation (κ=0.8-0.9) [80].

#### Quality of Life

The EQ-5D-5L is a generic utility-based health related quality of life questionnaire [81] with an MCID of 0.056 [82]. It consists of 5 questions covering the dimensions of mobility, self-care, usual activities, pain and discomfort, and anxiety and depression with 5 response options indicating no, mild, moderate, severe, and extreme problems for each dimension [83]. The EQ-5D-5L can define a total of 3125 health states which can be converted to a utility index anchored at 0 for a state being equal to dead, and 1 for full health using the Canadian Scoring function [84]. The utility index combined with life expectancy allows for the estimation of quality-adjusted life years (QALYs), a recommended generic outcome measure in health economic evaluation in Canada and other countries [85-87].

#### Self-Efficacy for Physical Activity

Participants will be asked to rate how confident they are that they could participate in moderate intensity physical activity for 150 minutes per week using a single question on a scale of 1 (not at all confident) to 10 (completely confident) [88].

#### Health Care Usage

Health care usage data to assess service use and cost effectiveness of the trial will be collected using administrative data accessible at the Institute for Clinical Evaluative Sciences (ICES) at McMaster University. Specifically, usage data will be obtained through the following databases: Ontario Health Insurance Plan, National Ambulatory Care Reporting System, and the Discharge Abstract Database, which are all housed at ICES McMaster. We will use standard person-level costing approaches established by ICES [89] to capture the formal component of direct health care costs. Health care usage data will also be collected using a case report form (CRF) to complement the ICES administrative data. If a variable is not available in an administrative database, the CRF will capture the variable and be included in the economic analysis using standard micro-level costing approaches. Health care usage variables that will be collected using the administrative databases and CRF are direct costs, including health care facility visits, hospitalizations, family doctor visits, specialist visits, tests and procedures, other health care services, and falls. The project leads will work with ICES scientists, a health economist, and an ICES Research Analyst. The administrative databases will be accessed once all of the clinical data has been collected.

#### Focus Groups

Our pilot study demonstrated perceived transformative aspects of the intervention that require further exploration and explication. Focus groups, following an interpretive descriptive approach, will be conducted [90] to identify possible aspects that enable participants to improve their mobility and become more successful self-managers and explore how these may differ in the Stepping Up intervention compared with the telephone-based coaching walking program and chair-based yoga program. Gender considerations will be explored to describe how changes in mobility self-efficacy and SM are related to gendered environments and gendered role expectations. Virtual focus groups (4-6 per group) will be conducted by a qualitative researcher. Participants will be invited to take part in the focus groups at the end of the 12-week intervention period. There will be a total of 4 focus groups for each of the 3 interventions for a total of 12 focus groups over the course of the study. Interviews will be audio-recorded, transcribed, and deidentified. Refer to Multimedia Appendix 2 for the interview guide.

#### Sample Size

The sample size calculation is based on the primary outcome measure, the 4MGS test. Small clinically meaningful change is 0.05 m/second on the 4MGS test in older adults [2]. We expect to observe minimal to no change in the chair-based yoga group (0 m/s), small but meaningful change in the telephone-based coaching walking group (0.05 m/s), and a large change in the Stepping Up group (0.12 m/s) [61]. Assuming a correlation between baseline and 12-week scores of 0.5, a mean baseline gait speed of 1.14 m/second, and a common SD of 0.22, a sample size of 66 per group (N=198) will have 80% power at the 0.05 significance level. To account for dropouts (20%), the planned total sample size is 249 (or 83 per group). Sample size calculations were performed using SAS (version 9.4; SAS Institute).

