Two randomized controlled trials (RCTs) examining the effect of task-oriented motor learning (TOML) exercise on mobility delivered to older persons (mean age 77.2, SD 5.5 years) showed greater improvement in energy cost of walking, gait quality, walking confidence, and physical function compared with persons who participated in impairment-focused exercise [24,25]. A recent large scale RCT (n=298) in senior residential apartments found a significant difference between an intervention focused on coordination and timing versus a seated strength and flexibility control. The between-group difference on the 6MWT was 17 m (*P*=.03) and between-group difference on gait speed measured using an instrumented walkway was 0.05 m/second (*P*=.02) [26]. Using a TOML approach facilitates the re-education of basic functional movement patterns to a wide variety of dynamic activities and targets more integrated aspects of balance and mobility.

Self-management (SM) has been promoted to increase healthy behaviors and manage symptoms for persons with chronic conditions [27]. Studies have examined the use of SM to deliver rehabilitation-based principles and manage musculoskeletal issues associated with chronic conditions [27-29], but SM has not been used to address changes in mobility.

According to our research, PCML has not been addressed by tailored primary prevention interventions that incorporate both TOML and SM. From 2014-2016, we undertook a pilot RCT (n=89) to compare an intervention that combined TOML exercise and mobility SM principles (Stepping Up) to an existing community-based fall prevention program. In the pilot, we established the feasibility and acceptability of the intervention as well as preliminary effects [30]. We now propose a fully powered RCT to demonstrate that the Stepping Up program will improve walking in persons with PCML.

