### Objectives

Our primary objective is to determine if a 12-week mobility program called Stepping Up is more effective than a telephone-based coaching walking program or a chair-based yoga program at improving walking speed, assessed using the Four-Meter Gait Speed (4MGS) test. Secondary objectives are to compare the effectiveness of the Stepping Up program to the telephone-based coaching walking program and the chair-based yoga program for the following outcomes: (1) gait speed at 24 and 36 weeks and (2) aerobic exercise capacity, dual-task cost, physical functioning (balance and strength), balance confidence, extent of community mobility, SM of mobility, and quality of life at 12, 24, and 36 weeks.

We will compare the cost-effectiveness of the Stepping Up program to the telephone-based coaching walking program and the chair-based yoga program with respect to health care usage costs (including hospitalizations and physician visits) and program-related costs over 36 weeks.

Focus groups will be conducted to discover how participants in the Stepping Up program develop their mobility skills in comparison to those in the telephone-based coaching walking program and chair-based yoga program.

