### Analysis

Baseline characteristics will be analyzed using descriptive statistics reported as mean (SD) or median (first quartile {Q1}, third quartile {Q3}) for continuous variables, depending on the distribution and count (%) for categorical variables. All analyses of primary and secondary outcomes will follow the intention-to-treat principle. The results will be reported as relative risk or odds ratio for binary outcomes or mean difference for continuous outcomes, with corresponding 95% CI and associated *P* values. All *P* values will be reported to 3 decimal places with those less than .001 reported as *P*<.001. All analyses will be performed using SAS 9.4. We will use multiple imputation to handle missing data [92].

To assess the effect of the intervention on the primary outcome (4MGS), we will conduct an analysis of covariance adjusting for age as a stratification variable and baseline value of 4MGS as a covariate. Secondary outcomes will also be analyzed using analysis of covariance, again using age as a stratification variable and baseline value for each outcome as a covariate. No interim analysis is planned.

We will conduct exploratory subgroup analysis for both the primary and secondary outcomes by including an interaction term between the subgroup variable (sex and age) and the treatment group variable. The multiple measures subgroup analyses will not be adjusted for multiple testing since they are exploratory.

Our hypothesis is that there will be reduced hospitalizations and physician visits for the intervention group compared with the control groups. Cost data is usually treated as nonparametric. Therefore, a Poisson or negative binomial distribution will be used to model the number of hospitalizations and physician visits by counts to determine the difference between the groups on relative intervention cost.

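### The stated 80% power does not cover Stepping Up versus telephone coaching, which has about 56% at 66 evaluable per group under the planned ANCOVA

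*Protocol article*

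**What the plan says.** The primary objective (Objectives) is to determine whether Stepping Up "is more effective than a telephone-based coaching walking program or a chair-based yoga program at improving walking speed". The Interventions section gives the two controls different roles: telephone coaching is the comparative-effectiveness control and chair yoga the attention control.

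The Sample Size section expects changes of 0 m/s with yoga, 0.05 m/s with telephone coaching and 0.12 m/s with Stepping Up. It assumes a baseline to 12-week correlation of 0.5 and "a common SD of 0.22", and concludes that "a sample size of 66 per group (N=198) will have 80% power at the 0.05 significance level". Allowing for 20% dropout gives 83 per group, 249 in all. It does not state the test, the contrast or whether the test is two-sided.

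For the primary outcome, the Analysis section says: "we will conduct an analysis of covariance adjusting for age as a stratification variable and baseline value of 4MGS as a covariate". The Results section reports that recruitment closed with 253 enrolled and that analysis starts in November 2025.

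**The concern.** One power figure is given for an objective that names two comparators, and the expected effects against them differ: 0.12 m/s against yoga but only 0.07 m/s against telephone coaching. A sample size that suits the first, or an overall test driven mainly by the first, need not suit the second.

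The comparative-effectiveness question is at stake. If Stepping Up performs exactly as assumed, a non-significant telephone comparison could still be close to an even chance. Reported beside an unqualified 80%, it could be taken to show that the programme is no better than telephone coaching.

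**Working it through.** **Inputs.** From Sample Size: means 0, 0.05 and 0.12 m/s; SD 0.22; correlation 0.5; alpha 0.05; 66 evaluable or 83 randomised per group. From Analysis: ANCOVA on baseline. My assumption: two-sided tests, since sidedness is not stated.

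**Standard deviations.**
- ANCOVA residual SD = 0.22 × √(1 - 0.5²) = 0.1905.
- Change-score SD = 0.22 × √(2 × (1 - 0.5)) = 0.22, the same as the raw SD.

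**Reproducing the plan's 66.**
- *Overall F test, SD 0.22.* The mean of the three changes is 0.0567 and the sum of squared deviations is 0.0072667. Noncentrality = 66 × 0.0072667 / 0.0484 = 9.91 with 2 and 195 df. Power is 80.5% (79.9% at 65), so 66 is the smallest n that reaches 80%.
- *Stepping Up v yoga, t test at 0.025, SD 0.22.* Noncentrality = 0.12 / (0.22 × √(2/66)) = 0.12 / 0.0383 = 3.13. Power is 80.6% (79.9% at 65), so this also gives exactly 66.
- *Stepping Up v the average of both controls, SD 0.22.* The difference is 0.12 - 0.025 = 0.095, and 64 per group reaches 80%.
- *Dropout.* 66 / 0.8 = 82.5, rounded up to 83; × 3 = 249.
- *Overall F test under ANCOVA.* Noncentrality = 66 × 0.0072667 / 0.0363 = 13.21. Power is 91%, and 50 per group would reach 80%. The stated 66 therefore takes no credit for the ANCOVA variance reduction.

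**Power by comparison.** SE = SD × √(2/n) and noncentrality = difference / SE, two-sided 0.05. For telephone under ANCOVA at 66: SE = 0.1905 × √(2/66) = 0.0332 and noncentrality = 0.07 / 0.0332 = 2.11.

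| Comparison | ANCOVA, n=66 | ANCOVA, n=83 | SD 0.22, n=66 | SD 0.22, n=83 |
|---|---|---|---|---|
| Overall F test | 91% | 96% | 80.5% | 89% |
| Stepping Up v yoga (0.12) | 95% | 98% | 87-88% | 94% |
| Stepping Up v telephone (0.07) | 55-56% | 65% | 44% | 53% |

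The small ranges reflect pairwise or pooled df. Further results for the telephone comparison:
- With Bonferroni 0.025 at n=66: 44% under ANCOVA, 33% on SD 0.22.
- With a one-sided 0.05 test at n=66: 68% under ANCOVA, 57% on SD 0.22.
- Both comparisons significant at two-sided 0.05, n=66 (simulation): 55% under ANCOVA, 43% on SD 0.22.
- For 80% power at 0.07 m/s: 118 evaluable per group under ANCOVA, or 157 on SD 0.22.
- Smallest difference with 80% power at n=66: about 0.094 m/s under ANCOVA, above the expected 0.07.

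**Precision.** The expected 95% CI half-width under ANCOVA at 66 per group is 1.97 × 0.0332 = 0.065 m/s. For the upper limit to fall below 0.05 m/s, the estimate would have to be below 0.05 - 0.065 = -0.015 m/s, that is, in favour of telephone coaching.

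**The case against.** **No stated figure is miscalculated.** Both 66 and 83 reproduce. That stands: the fault is what the 80% is taken to cover, not the arithmetic behind it.

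**The test is unknown.** A reader might infer that the 80% belongs to the overall F test. That is plausible, because it uses all three means at the stated alpha, but the article does not say so, and the Bonferroni test against yoga also gives exactly 66. Neither reading powers the telephone comparison.

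**Baseline adjustment.** A reader might infer that the calculation ignored baseline. At a correlation of 0.5 the raw and change-score SDs are equal, so this cannot be established. Only the absence of the ANCOVA gain is certain, and that is conservative.

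**Size.** A reader might attach 44-56% to the planned enrolment. That range belongs to 66 evaluable per group, and its low end to an analysis other than the planned ANCOVA. With 83 analysed under ANCOVA, power is about 65%. Follow-up is offered to people who stop their intervention, and missing data will be multiply imputed. Imputation does not restore lost information, so 66 remains a fair planning case.

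**The word 'or' in the objective.** Read as a win against either control, power is about 96% under ANCOVA and 89% on SD 0.22. Yoga alone supplies 95% and 87-88% of that, so this reading says almost nothing about telephone coaching.

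**A borrowed effect.** The Background cites a trial in which the "between-group difference on gait speed measured using an instrumented walkway was 0.05 m/second", and a reader might use that as the likely telephone difference. Its control was seated strength and flexibility exercise, not walking coaching, so it does not support that use.

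**A higher correlation.** About 0.77 would give 80% for the telephone comparison under ANCOVA at 66 per group (0.69 at 83). The protocol assumes 0.5.

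**The analysis plan may define the contrasts.** It may, but no definition there makes 66 per group deliver 80% for a 0.07 m/s difference on these assumptions.

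**Conclusion.** The point holds in this form: the unqualified 80% does not apply to one of the two comparisons named in the primary objective. For Stepping Up against telephone coaching, power under the planned ANCOVA is about 56% at 66 evaluable per group and about 65% with all 83. Without the ANCOVA variance reduction it is 44% and 53%. These figures rest on a 0.07 m/s difference, SD 0.22, correlation 0.5, two-sided 0.05 and no multiplicity adjustment.

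The trial as a whole should not be called underpowered on this ground. The overall test and the yoga comparison both exceed 80% on the same assumptions. How a null telephone result would actually be read is a risk, not a certainty, since the Analysis section already commits to mean differences with 95% CIs.

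**What to change.** Restate the power by comparison, tied to the planned ANCOVA and with its assumptions written out. For example: assuming changes of 0, 0.05 and 0.12 m/s, SD 0.22, correlation 0.5 and two-sided 0.05 without multiplicity adjustment, 66 evaluable participants per group give about 91% power for the overall test, 95% for Stepping Up against yoga and 56% for Stepping Up against telephone coaching. If a multiplicity adjustment is planned, give the adjusted figure instead; with Bonferroni 0.025 the telephone comparison has about 44%.

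State before analysis that the telephone comparison will be interpreted by its 95% CI (expected half-width about 0.065 m/s) against the 0.05 m/s meaningful change, and that a non-significant result will not be read as equal effectiveness.

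The cost is one paragraph in the protocol or analysis plan, carried into the final report. It needs no extra participants, data or change of estimator. The stated power for one comparison becomes less favourable.

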### Recruitment

Participant recruitment will occur from August 2021 to January 2025, and follow-up assessments will be completed by October 2025. Refer to Figure 1 for the SPIRIT schedule of enrolment, interventions, and assessments. Participants will be recruited through advertisements in local newspapers and social media sites (ie, Facebook and Instagram, Meta). We will send out promotional material about the study in e-Newsletters of agencies that cater to older adults (ie, senior research centers, university retiree groups, and local Councils on Aging), and advertise on the websites of local libraries and Active Aging Canada. Posters and postcards will be displayed in local Young Men’s Christian Associations (YMCAs), helping to spread the word and raise awareness for the study. The ads will be created using design elements that appeal to older adults and will include information about how to contact the research team. We will recruit over a period of 42 months (recruitment rate of 6-8 participants per month), and we will deliver the interventions to groups of 5-7 participants in 12-week sessions.

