### Study Setting

The Stepping Up and chair-based yoga interventions will be delivered in synchronous online classes, and the telephone-based coaching walking intervention will be delivered by phone. This trial was initially planned for in-person delivery but switched to online delivery due to COVID-19 restrictions.

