### Randomization

The unit of randomization will be the participant, and the randomization process will use computer generation of group assignment using the REDCap (Research Electronic Data Capture; Vanderbilt University) randomization module. REDCap is a secure web application designed to support data capture for research studies [91]. Participants will be stratified by age (55-64 years or 65-75 years). An allocation table will be created and uploaded to the REDCap randomization module by a statistician not involved in the RCT. Using a 1:1:1 allocation ratio, we will block the randomization with variable block sizes of 3, 6, and 9. The RC will not have access to the allocation table. Once participant consent is obtained and the baseline assessment is complete, the RC will access the randomization module in REDCap to enter the participant strata value (age category) and receive the group allocation.

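### Two of the three arms are taught in classes of 5-7, but the stated primary ANCOVA treats all participants as independent, so type I error exceeds 5% if the within-class correlation is positive

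*Protocol article*

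**What the plan says.** **Allocation.** The Randomization section states: "The unit of randomization will be the participant". Allocation is 1:1:1 in variable blocks, stratified by age.

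**Delivery.** Study Setting says: "The Stepping Up and chair-based yoga interventions will be delivered in synchronous online classes". For the third arm, "the telephone-based coaching walking intervention will be delivered by phone". The Recruitment section gives the class size: "we will deliver the interventions to groups of 5-7 participants in 12-week sessions".

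**Analysis.** For the primary outcome, "we will conduct an analysis of covariance adjusting for age as a stratification variable and baseline value of 4MGS as a covariate". The secondary outcomes get the same form of model. The article mentions no class or instructor term, random effect or cluster-robust error.

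**Sample size.** The inputs are expected changes of 0, 0.05 and 0.12 m/s, a correlation of 0.5, an SD of 0.22, 80% power and a 0.05 level. They give 66 per group, and 83 per group after 20% dropout. No ICC or design effect appears.

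**The concern.** Randomizing individuals and then teaching two arms in groups gives a partially nested design. Members of a Stepping Up class share an instructor, a monitoring physiotherapist, group self-management sessions and each other's company. Members of a yoga class share an instructor and each other. Any of these can make 12-week outcomes within a class more alike than outcomes across classes. The telephone arm has no classes.

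An ANCOVA without a class term estimates the standard error as if every participant gave independent information. With a positive class correlation that standard error is too small. The effect is unequal: both arms are clustered in Stepping Up versus yoga, but only one is in Stepping Up versus telephone. At stake are the P value and confidence interval for gait speed and for each continuous secondary outcome analyzed the same way.

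**Working it through.** **1. Reproduce the stated sample size.** With correlation 0.5, the SD of change is 0.22 × √(2 × (1 − 0.5)) = 0.22. For a three-group overall F test with means 0, 0.05 and 0.12, the squared deviations from the mean sum to 0.00727. At 66 per group the noncentrality is 66 × 0.00727 / 0.0484 ≈ 9.9, which gives 80.5% power with 2 and 195 df. Dropout: 66 / 0.8 = 82.5, rounded up to 83, and 3 × 83 = 249. The stated figures match exactly with independent participants, that is, a design effect of 1.

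**2. Evaluable participants per class.** If 5-7 describes evaluable participants, take m = 6. If it describes class size at enrolment, 83 / 6 ≈ 14 classes, and 66 / 14 ≈ 4.7 evaluable per class. Both are carried forward.

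**3. Type I error of the unadjusted comparison.** The ICC is an assumption, because the article gives none. It means the class-specific correlation of the outcome after adjustment for baseline and age.
- Design effect: DE = 1 + (m − 1) × ICC.
- Variance ratio: v = DE for Stepping Up versus yoga, and v = (DE + 1) / 2 for Stepping Up versus telephone.
- Actual two-sided level: 2 × (1 − Φ(1.96 / √v)).

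Example with m = 6 and ICC 0.05: DE = 1.25. Against yoga, 1.96 / √1.25 = 1.753, giving 8.0%. Against telephone, v = 1.125 and 1.96 / √1.125 = 1.848, giving 6.5%.

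| Assumed ICC | DE (m = 4.7 to 6) | Level vs yoga | Level vs telephone |
|---|---|---|---|
| 0 | 1.00 | 5.0% | 5.0% |
| 0.02 | 1.07 to 1.10 | 5.9-6.2% | 5.4-5.6% |
| 0.05 | 1.19 to 1.25 | 7.2-8.0% | 6.1-6.5% |
| 0.10 | 1.37 to 1.50 | 9.4-11% | 7.2-8.0% |

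Simulation (40,000 replicates, 66 per arm, two clustered arms and one unclustered) agreed with the m = 6 formula values. The unadjusted overall F test, which is the test that reproduces the sample size, rejected in about 5.8%, 7.6% and 10.7% of null trials at m = 6 and ICC 0.02, 0.05 and 0.10.

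**4. Power.** The ANCOVA residual SD is 0.22 × √(1 − 0.5²) = 0.1905. At 66 per arm the unclustered standard error is 0.1905 × √(2/66) = 0.0332.
- Difference 0.12 (vs yoga): 0.12 / 0.0332 = 3.62, power about 95%. At ICC 0.05 and m = 6 the standard error is 0.0332 × √1.25 = 0.0371, power about 90%.
- Difference 0.07 (vs telephone): 0.07 / 0.0332 = 2.11, power about 56%. With clustering the standard error is 0.0332 × √1.125 = 0.0352, power about 51%.

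**The case against.** **The inflation is conditional.** A reader might infer that type I error certainly exceeds 5%. The documents do not support that. They give no ICC, at 0 there is no inflation, and at 0.02 it is about one percentage point or less. Several features could keep the ICC low: exercises are tailored to the individual, all participants in Stepping Up can use the same website material, and the outcome is an individual timed walk scored by a blinded assessor. If one instructor taught every class in an arm, the instructor would add no between-class variance. Calendar effects common to all arms are largely balanced by blocked allocation. All of this stands and limits the likely size. It does not show that the ICC is zero, and the stated model could not reveal it.

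**Clustering is not the main reason for low power against telephone.** The 51% figure might be read that way. Without clustering it is already 56%, because the assumed difference is only 0.07 m/s.

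**Pairwise tests are not named.** The Analysis section specifies an ANCOVA without saying which contrasts are tested. The Objectives compare Stepping Up with each comparator, so both contrasts are shown, and the overall F test is also inflated.

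**A separate analysis plan may handle this.** It may, and its absence here is not a finding. The point is that the article states a model, and that model omits the class structure the article itself describes.

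**Conclusion.** The point holds in conditional form. The stated ANCOVA and sample size ignore partial nesting in two of the three arms, and the analysis is anti-conservative for any positive class-specific ICC. Under the assumed range the effect runs from none (ICC 0) to roughly double the nominal level against yoga (ICC 0.10), and is always smaller against telephone. The result assumes that the classes act as stable groups over the 12 weeks, which the Recruitment wording suggests but does not say outright, and that telephone participants are independent. Severity: should fix, with moderate confidence, because the direction is clear but the size is unknown.

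**What to change.** Before analysis begins, replace the plain ANCOVA for gait speed and the continuous secondary outcomes with a partially nested linear mixed model:
- Fixed effects: arm, baseline value and age stratum.
- Random class effect in Stepping Up and yoga only, with class defined as assigned, whether or not the participant attended.
- Small-sample degrees of freedom (Kenward-Roger or Satterthwaite), since there are only about 14 classes per arm.
- The estimated ICC reported, and the multiple imputation made compatible with the class structure.

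An arm-specific residual variance and a therapist effect in the telephone arm are optional sensitivity analyses.

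The model runs in the planned SAS software and needs one class identifier, which the trial must hold to run the classes. Enrolment is complete at 253, so this changes the analysis only, not the sample size. If the ICC is near zero, the results will hardly move. The costs are slightly wider intervals and recoding of class identifiers so that they do not reveal the arm. Recoding can keep Stepping Up and yoga masked from each other, but the arm without classes will be recognizable from the model, so the code should be fixed before allocation is attached to outcomes.
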